## Analysis Plan

- 6 We hypothesize that in the 9 months following their index overdose, patients exposed to the MROT will: H1: be more likely to initiate MAT (Primary outcome) H2: have fewer non-fatal ODs (Primary outcome) H3: be retained in MAT longer (Secondary outcome) H4: be less likely to die of a subsequent OD (Secondary outcome) All analyses will be conducted using the intent-to-treat principle. Demographic and descriptive statistics will be calculated at baseline and at 9-months following the index overdose. The baseline characteristics and main outcomes between the intervention and control groups will be compared using the chi-square test and the two-sample t-test. To test the hypotheses with the dichotomous outcome (initiation of MAT) and the ordinal outcome (incidence of non-fatal OD) we will use generalized linear mixed effects models (SAS PROC GLIMMIX) and Bayesian hierarchical models (SAS PROC MCMC) to account for the complexity of non-normal outcomes and intricate cluster effects due to the interdependence of patients within hospitals. The sensitivity analysis for Bayesian hierarchical models will also be performed. For the time to treatment, retention in treatment, and death due to subsequent OD outcomes, we will apply marginal Cox models (SAS PROC PHREG) to estimate the main effect of intervention exposure and use the robust sandwich covariance matrix estimation approach to account for the intracluster dependence. Individual demographic information including age, race, sex, drug of choice (heroin vs. prescription opioids), insurance type (e.g., Medicaid vs. private), and location of residence (urban vs. rural) will be included in the mixed effects models and marginal Cox models to control for potential confounding effects. We will obtain records from the SSA for 9 months prior to the index overdose for all participants, to allow us to control for prior history of non-fatal overdose and MAT utilization. Other covariates at the hospital level will include location (e.g., Northern Nevada vs. Southern Nevada, rural vs. urban) and hospital type (e.g., regional, university, trauma center, etc.). In addition to the statistical approach described above, we will also employ a propensity score (PS) matching approach as a secondary analysis. PS matching is particularly well-suited to "natural experiments" in which assignment to condition cannot be manipulated, such as the implementation of state programs. The approach involves calculating the probability of assignment to a treatment or exposure using logistic regression in which we enter observed characteristics that could influence assignment. In this case, known characteristics of patients such as age, sex, location of residence (rural vs. urban), previous history of overdose, or previous history of MAT enrollment. The PS reduces the large set of possible covariates that could influence selection into the intervention or control

condition into a single summary variable. The PS represents the a priori probability that patients will be in the intervention or control condition; patients with similar PS's are assumed to have the same distribution of covariates. After calculation of the PS, intervention and control patients are 'matched' based on the overlap in their PS's, the distribution of covariates in the two groups compared, and success of the matching evaluated. Finally, the outcomes analysis is conducted using regression approaches as described above using the matched set of patients.

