#### 4.1 Sample Size:

In 2017, the six participating hospitals reported a total of 308 opioid-related poisoning visits to the ED, representing 37% (308/829) of the total visits statewide. Those numbers are highly conservative, because they are restricted to a small set of ICD-10 billing codes (primary diagnosis of T40.0, T40.1, T40.2, T40.3, T40.4, and T40.6). Other research found that using only ICD-9/10 billing codes related to opioid poisoning results in low sensitivity (as low as 25%). Additionally, rates of opioid-related visits have increased significantly over the past several years in Nevada (+12% 2010-2015, and +22% 2014-2015). Therefore, we anticipate that the actual number of intervention participants will be significantly higher. Using the findings from the sensitivity analysis above, we estimate the possible number of opioid-related poisonings for the 6 intervention hospitals to be 1232. The upper bound of the possible number of participants is represented by the total set of opioid-related ED encounters, which was 2635 in the six intervention hospitals in 2017, representing 37% (2635/7125) of encounters statewide. We anticipate 5% of control patients will access MAT compared to 33% of intervention patients. We anticipate that 7-12% of control patients will experience a non-fatal overdose in the 9 months following their index overdose, and that will be reduced by around 47% among intervention participants. According to unpublished data from the SSA, we anticipate 10% of control participants will die of an overdose in the next year compared to 5% in intervention participants.

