#### 4.2 Sample Size Rationale:

The alpha significance level of the power analysis is set to 0.05. At least 82% power will be achieved to detect a small effect size of 0.2 under the anticipated conservative sample size. Under different assumptions of effect size, such as medium effect size of 0.5 and large effect size of 0.8, our analysis strategy will have at least 99% power. For reasonably anticipated sample size 3316 (1232 intervention and 2084 control), at least 99% power will be achieved to detect as small as 0.1 effect size. Therefore, a very conservative sample of 829 (308 intervention and 521 control) patients will be sufficient to evaluate the primary outcomes. R package pwr was used for power analysis. To be our best knowledge, very few existing power analysis approaches can be applied to hierarchical models. In addition to the primary aims of the proposal, data will be used to develop a statistically reliable and computationally efficient power analysis procedure for hierarchical models and implement the proposed approach in an R package and a SAS macro.

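### The 9-month look-back is used only for prior overdose (source unstated) and prior MAT; if overdose history comes from billing codes, most of its confounding could remain, and prior opioid-related and total ED use are not named as covariates

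*Protocol*

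**What the plan says.** Section 3 (Design Plan) describes a quasi-experiment. Intervention patients are those at the six hospitals who have contact with the outreach team; controls come from hospitals that have not yet adopted it.

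Section 6 (Analysis Plan) adjusts for age, race, sex, drug of choice, insurance, residence, hospital location and hospital type. It also obtains nine months of pre-index state records "to allow us to control for prior history of non-fatal overdose and MAT utilization". The propensity score list, given as examples, repeats both histories: "previous history of overdose, or previous history of MAT enrollment". Neither list names prior opioid-related encounters or prior ED visits in general.

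Section 4.1 (Sample Size) reports other research in which "using only ICD-9/10 billing codes related to opioid poisoning results in low sensitivity (as low as 25" per cent).

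Section 4 (Sampling Plan) names three linked databases: hospitalization, mortality and MAT participation. Section 5 (Measured Variables) expects the overdose reporting law in force from July 1, 2017 to make overdoses identifiable in state surveillance data.

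**The concern.** Earlier overdose is an obvious candidate confounder for the two overdose hypotheses. The arms can differ in it by hospital and by which patients the team reaches. The protocol does not say whether prior overdose will be read from hospital diagnosis codes, from the mandatory report, or from both. Of the three databases it lists, only the hospitalization file would hold ED-treated overdoses, and the mandatory report is not on the list.

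If poisoning codes are the source, the protocol has itself cited evidence that they can miss up to three quarters of cases. Most patients with a true prior overdose would then be classed as having none. Regression or matching on that flag would leave most of the confounding by true history in place. A post-matching comparison sees only the flag, so it could look well balanced while true history still differed.

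The same look-back should also hold broader markers of earlier opioid-related care, and the plan does not name them.

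**Working it through.** **1. Does the protocol rely on the 25% figure?** Yes, for its sample size. Section 4.1: "the six participating hospitals reported a total of 308 opioid-related poisoning visits to the ED, representing 37% (308/829"), and then "we estimate the possible number of opioid-related poisonings for the 6 intervention hospitals to be 1232". Check: 308 / 0.25 = 1232. The total in section 4.2, "For reasonably anticipated sample size 3316 (1232 intervention and 2084 control"), follows in the same way: 521 / 0.25 = 2084 and 829 / 0.25 = 3316. All three reproduce exactly.

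**2. How many prior overdoses would such codes find?** The protocol gives no pre-index prevalence. As an assumption I borrow its post-index control figure, "7-12% of control patients will experience a non-fatal overdose in the 9 months following their index overdose". Among 3316 patients:
- true prior overdoses: 3316 × 0.07 = 232 to 3316 × 0.12 = 398
- recorded at 25% sensitivity: 58 to 100
- true prevalence p among those recorded as negative, 0.75p / (1 − 0.25p): 5.3% at p = 7% and 9.3% at p = 12%.

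**3. How much confounding does the flag remove?** Assumptions: no true intervention effect, specificity 1, the same sensitivity in both arms, and a risk ratio r for the outcome given true prior overdose.
- Crude risk ratio = [1 + (r − 1)p1] / [1 + (r − 1)p0], where p1 and p0 are the true prevalences in the intervention and control arms.
- Adjusted risk ratio = Mantel-Haenszel over the recorded strata, arms 1232 and 2084. It stands in for the planned models.
- Share removed = 1 − ln(adjusted) / ln(crude).

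Example with p1 = 7%, p0 = 12%, r = 3 and sensitivity 25%:
- Crude: 1.14 / 1.24 = 0.919.
- Recorded-positive stratum: risk ratio 1, because everyone in it is truly positive.
- Recorded-negative stratum: (1 + 2 × 0.0534) / (1 + 2 × 0.0928) = 0.934.
- Pooled: 0.937.
- Share removed: 1 − ln 0.937 / ln 0.919 = 23%.

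Other assumed scenarios at 25% sensitivity:

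| True prevalence, intervention vs control | r | Crude RR | Adjusted RR | Bias removed |
|---|---|---|---|---|
| 7% vs 12% | 2–4 | 0.955–0.890 | 0.965–0.913 | 22–23% |
| 12% vs 7% | 2–4 | 1.047–1.124 | 1.036–1.094 | 23% |
| 10% vs 20% | 3 | 0.857 | 0.885 | 21% |
| 20% vs 35% | 2–4 | 0.889–0.780 | 0.908–0.816 | 18% |
| 35% vs 20% | 2–4 | 1.125–1.281 | 1.099–1.220 | 20% |

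Over these scenarios the share **left in place** is about 77–82% at 25% sensitivity, 52–60% at 50% and 27–34% at 75%. It depends mainly on sensitivity, and only slightly on the assumed imbalance and risk ratio. Using arms of 308 and 521 gives the same figures.

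**4. Can a wider measure be counted?** Section 4.1 gives the total of opioid-related encounters, "which was 2635 in the six intervention hospitals in 2017, representing 37% (2635/7125) of encounters statewide". Against coded poisonings the ratio is 2635 / 308 = 8.6 in the six hospitals and 7125 / 829 = 8.6 statewide. This shows that the state can identify such encounters. It does not show how well they stand in for true prior overdose.

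**The case against.** Several points on the other side stand.

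- **The source is not stated to be billing codes.** Section 5 expects mandatory reporting to identify overdoses, which would make sensitivity far better than 25%. However, section 4 does not list that report among the linked databases, and section 5 raises it when defining the outcome. The source is undefined, so the calculation is conditional on it.
- **25% is a floor.** The protocol cites it from other research and uses it to scale the sample. At 75% sensitivity about 66–73% of the bias is removed.
- **Other covariates also carry overdose risk.** A reader might infer that overdose history is the only adjustment for prior risk, and that it is nearly powerless. The protocol does not support that: MAT history, drug of choice, insurance, residence and demographics are adjusted for too, and even at 25% sensitivity about a fifth of the bias is removed.
- **The imbalance is assumed.** At 7% against 12% the residual bias is about 4–9%. A reader might infer that confounding could account for the planned 47% reduction (risk ratio 0.53); none of the scenarios comes near that.
- **The benefit of the added covariates is unproven.** Eligibility already includes an opioid use disorder diagnosis, so a broad opioid-encounter flag may mark chronic contact more than overdose.
- **Covariate detail can be left to an analysis plan.** The propensity list is open, and a balance check after matching is already planned. But for the regression the protocol states a purpose for the look-back, and that purpose stops at two histories.

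**Conclusion.** The point holds in a conditional form. The protocol relies on adjustment in a non-randomised comparison, states only two uses for its look-back records, and does not say how the one direct measure of earlier overdose is obtained. If that measure rests on poisoning codes at the cited worst-case sensitivity, roughly four fifths of the confounding by true prior overdose stays, and balance on the recorded variable would not reveal it.

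That share assumes perfect specificity and equal sensitivity in both arms, and it leaves aside what the other covariates absorb. The resulting bias in the effect estimate cannot be fixed from the protocol, because neither the imbalance nor its direction is given. It would be modest at the lower assumed prevalences and larger at the higher ones (0.82–0.91 or 1.10–1.22 for 20% and 35%). That is enough to distort an estimate and its interval, and it does not show that the planned effect is spurious.

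**What to change.** - State whether prior overdose is taken from hospital codes, the mandatory overdose report, or both. If the report is used, add it to the linked databases in section 4.
- From the same nine-month look-back, derive (a) any prior opioid-related ED or hospital encounter, in any diagnosis position, and (b) the number of prior ED visits of any cause.
- Enter both in the mixed, Bayesian and Cox models and in the propensity score. Keep prior overdose and prior MAT history.
- Check balance on the added variables after matching.

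The cost is two more derived covariates and a few lines of text. No new database is needed for them, provided that the extract already requested includes all-cause ED visits, which should be confirmed with the state. How much residual confounding they would remove cannot be quantified from the protocol.

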#### 6.1 Inference Criteria:

A p-value of  $<0.05$  will be considered statistically significant. 95% Confidence Intervals will be reported and all hypothesis testing will be two-sided. All analyses will be performed using SAS Version 9.4 for Windows.

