## Description

The over-arching goal of this research is to test the effectiveness of a Mobile Recovery

- 1 Outreach Team (MROT) intervention for opioid overdose and/or opioid use disorder patients treated in Nevada's Emergency Departments (EDs). MROT's will provide peer coaching and mentorship, referrals to medication-assisted treatment (MAT), and opioid overdose education and naloxone as part of the State's SAMHSA STR Program. We will accomplish the research goal through the following two aims: (1) Determine the effectiveness of the MROT on (a) subsequent overdose, and (b) MAT uptake among patients presenting to a hospital ED for opioid overdose, and (2) Evaluate the MROT implementation and fidelity through comprehensive process evaluation. In addition, the research will examine the feasibility and acceptability of a mobile team intervention model in rural Nevada. Because we know Nevada has a unique landscape with many cities located in rural/frontier areas where a traditional model may not be feasible, we will expand our feasibility/acceptability research and outcomes evaluation to include examining the impact of alternative models in hospitals in the rural/frontier regions of Nevada.

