### Measured Variables

- 5 Intervention vs. Standard of Care: The exposure of interest is whether patients receive the MROT program or standard of care. Standard of care will be defined as receiving standard discharge instructions and a passive referral to local services. There are 2 primary outcomes

of interest that will be observed in the 9 months following the patient's initial contact with the MROT: MAT treatment initiation, and non-fatal overdose. Secondary outcomes of interest include MAT treatment retention and fatal overdose. All outcome variables will be measured using data that are available within the SSA databases and which will be provided to the research team in a linked, de-identified data set. Non-fatal overdose will be defined as experiencing an overdose that is treated by ED personnel in the six months subsequent to the initial contact with the MROT. In 2017 Nevada passed AB474, new opioid-related legislation that classified opioid overdose as a reportable condition. This law took effect July 1, 2017 and requires that ED clinicians make a name-based report to the public health authority when they treat an opioid overdose. This mandate should ensure that opioid overdoses are identified in the state surveillance databases. MAT treatment uptake will be measured in three ways. We will obtain records from the SSA that contain information about all patients enrolled in MAT through a state-funded or state-certified provider. First, to measure treatment uptake we will define a dichotomous variable representing whether patients enrolled in a MAT program. Second, we will define "time to treatment" as the time elapsed between the index overdose and enrollment in the MAT program. Third, we will follow MAT patients for 9 months and determine the duration of treatment participation for enrolled patients. Fatal overdose will be defined as a death of a patient that is determined to be opioid related (ICD-10 codes X42, X44, Y12, Y14, T40.0 – T40.6), as reported in the electronic death registry system. We will include all intentional, unintentional, and undetermined deaths in the initial analysis, and will conduct sub-analyses in which only unintentional and undetermined deaths are included.

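### Two primary outcomes are each tested at two-sided 0.05 with no rule for combining them; if either may carry effectiveness, the two-sided family-wise error on the primaries is about 8-10%.

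*Protocol*

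**What the plan says.** Section 5 (Measured Variables) states "There are 2 primary outcomes" and names them as MAT initiation and non-fatal overdose. Section 6 (Analysis Plan) carries them as "H1: be more likely to initiate MAT (Primary outcome) H2: have fewer non-fatal ODs (Primary outcome") and adds two further hypotheses, "H3: be retained in MAT longer (Secondary outcome) H4: be less likely to die of a subsequent OD (Secondary outcome").

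Section 6.1 (Inference Criteria) then sets one threshold for everything: p below 0.05 "will be considered statistically significant. 95% Confidence Intervals will be reported and all hypothesis testing will be two-sided". The power section uses the same level: "The alpha significance level of the power analysis is set to 0.05".

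The aim in section 1 (Description) is to "Determine the effectiveness of the MROT on (a) subsequent overdose, and (b) MAT uptake among patients presenting to a hospital ED for opioid overdose". It does not say whether one or both results are needed. No section gives an alpha split, a testing order or a gatekeeping step. The H-numbers cannot stand in for an order: H2 is retention and H3 is non-fatal overdose in section 2 (Hypotheses), and the two are exchanged in section 6.

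**The concern.** With two primaries each judged at 0.05 and no rule joining them, the document allows either significant result to be presented as showing that the mobile outreach intervention works. The error level of that conclusion is then not the stated 5%. The two outcomes could well diverge: one is a process outcome with a very large expected difference, the other a patient outcome with a much smaller one. The plan does not say what would be concluded if only one of them were significant, so that choice could be made after the results are known.

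**Working it through.** **Inputs.** From sections 5, 6 and 6.1: two primaries, two-sided 0.05 each. From 4.1: MAT access 33% versus 5%; control non-fatal overdose 7-12%, reduced by about 47%. From 4.2: 308 intervention and 521 control patients (829), or 1232 and 2084 (3316). Assumed, because the protocol gives neither: the correlation between the two test statistics (0 to 0.75) and the variance inflation from hospital clustering (1, 6, 10). The error rates assume one test per primary that holds its nominal level.

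**The plan's own figure.** Section 4.2 states "At least 82% power will be achieved to detect a small effect size of 0.2 under the anticipated conservative sample size". Normal approximation at 308/521: Φ(0.2/√(1/308 + 1/521) − 1.960) = 79.5%. An equal split of 829 gives 82.1%. So 82% is reproduced only with equal groups. That is a separate matter, but it confirms that the calculation used the full 0.05. At 0.025 the two values become 70.6% and 73.8%. The protocol states no family-wise error rate.

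**Family-wise error on the two primaries, both nulls true.** With independent tests:
- either direction: 1 − (1 − 0.05)² = 9.75%
- in the intervention's favour only: 1 − (1 − 0.025)² = 4.94%

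With correlation ρ and c = 1.960, the two-sided rate is 1 − ∫[Φ((c − √ρ·x)/√(1−ρ)) − Φ((−c − √ρ·x)/√(1−ρ))]² φ(x) dx. The favourable-direction rate drops the second Φ term.

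| ρ | either direction | in favour only |
|---|---|---|
| 0 | 9.75% | 4.94% |
| 0.5 | 9.07% | 4.54% |
| 0.75 | 8.10% | 4.05% |

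The references are 5% and 2.5%, so the ratio is about 1.6 to 2.0 on either scale.

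**Cost of control.** Pooled test of two proportions: power = Φ((d − z·SE₀)/SE₁), where SE₀ uses the pooled rate, SE₁ the separate rates, and z = 1.960 at 0.05 or 2.241 at 0.025.

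*MAT initiation, 308/521:* d = 0.28, SE₀ = 0.0259, SE₁ = 0.0284. At 0.025: (0.28 − 2.241 × 0.0259)/0.0284 ≈ 7.8, so power is over 99.9%. Multiplying the variances by 6 gives 97.6% (96.2% with unpooled variance); by 10, 85.7% (80.8%).

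*Non-fatal overdose, 308/521, independent patients:*
- 7% versus 0.53 × 7% = 3.71%: d = 0.0329, SE₀ = 0.0168, SE₁ = 0.0155. Power is 50.1% at 0.05 and 38.1% at 0.025.
- 12% versus 6.36%: d = 0.0564, SE₀ = 0.0215, SE₁ = 0.0199. Power is 76.4% at 0.05 and 66.1% at 0.025.

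An unpooled variance gives 56-81% falling to 45-72%, so the method matters; the pooled values are used here. At 1232/2084 overdose power stays above 96% even at 0.025.

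**What Holm does.** The smaller p-value is tested at 0.025 and, if that is significant, the other at 0.05. With both nulls true the two-sided family-wise error is 4.94% at ρ = 0 and 4.65% at ρ = 0.5. Overdose is tested at the full 0.05 whenever the MAT p-value is below 0.025, which has the MAT power shown above.

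**The case against.** The strongest reply is that the protocol defines no pooled effectiveness conclusion. Section 1 can be read as two outcome-specific questions, each with its own 0.05, which is defensible in a non-randomised programme evaluation. It can also be read as requiring both, in which case no adjustment is needed. This stands in part: the defect is an undefined success rule, and the 8-10% is conditional on either primary being sufficient.

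A second reply is that multiplicity procedures often sit in a statistical analysis plan, which is not shown. That limits the severity but does not remove the point. Section 6.1 fixes a flat threshold, and a later document would have to override it.

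Two stronger readings are tempting and are not supported:
- A reader might take 9-10% as the chance of falsely claiming that the intervention works. That figure counts significance in either direction, including apparent harm. The chance of a false favourable result on the primaries is about half of it.
- A reader might extend the family to all four hypotheses and quote 16-19%. Retention and fatal overdose are labelled secondary, and no rule in the protocol lets a secondary outcome alone carry effectiveness.

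**Conclusion.** The point holds for the two primaries only. As written, each is declared significant at two-sided 0.05 with no allocation, order or both-must-succeed condition. If either may support effectiveness, the two-sided family-wise error is about 8-10% instead of 5%, or about 4-5% instead of 2.5% in the intervention's favour. The size rests on an assumed correlation of 0.75 to 0 (it would be lower if the correlation were higher) and on both tests holding their nominal level. It should be corrected because the plan leaves the success criterion open and the correction is cheap on the protocol's own figures.

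**What to change.** In section 6.1, replace the blanket threshold for the primaries with one of the following; the choice is the sponsor's.

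1. Family-wise two-sided 0.05 by Holm's method: the smaller p-value at 0.025, then the other at 0.05.
2. A fixed sequence at two-sided 0.05: MAT initiation, then non-fatal overdose only if MAT initiation is significant.
3. Effectiveness is claimed only if both primaries are significant at 0.05.

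Report the secondary outcomes as supportive, with 95% confidence intervals. Refer to outcomes by name, because H2 and H3 differ between sections 2 and 6.

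The cost is one paragraph, with no extra patients or data. Under option 1 overdose is tested at essentially the full 0.05: MAT power at 0.025 is over 99.9% with independent patients, about 96-98% with an assumed variance inflation of 6, and 81-86% with 10. Under options 2 and 3 a failure on MAT initiation would block a confirmatory claim on overdose. Under option 3 a failure on overdose would also block the overall claim, so its power at 308/521 is essentially that of overdose alone (50-76% with independent patients). A plain Bonferroni split is the least attractive choice: overdose power would fall from 50-76% to 38-66%.
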